## 13. ETHICAL AND REGULATORY CONSIDERATIONS

### 13.1. ICH-GCP

The study will be conducted in accordance with the protocol and applicable International Conference on Harmonisation (ICH) GCP guidelines.

Date and version No: 18th July 2019, Version 4.2

### **13.2. Approvals**

The protocol, protocol amendments, ICF and the PIS will be submitted to the OxTREC, and host institution (MRCG and Ethics committee, CMC, Vellore) for written approval. Additionally, approvals will also be sought from Indian Council of Medical Research (ICMR) and the Medical control agency, The Gambia. The Investigator will submit and, where necessary, obtain approval from the above parties for all substantial amendments to the original approved documents.

### **13.3. Participant Confidentiality**

The study staff will ensure that the participants' anonymity is maintained. The participants will be identified only by a participant ID number on all study documents and any electronic database. All documents will be stored securely and only accessible by study staff and authorised personnel. The study will comply with the Data Protection Act, which requires data to be anonymised as soon as it is practical to do so. Personal data will be not be linked to research data and maintained in separate files which are password protected and accessible only to authorized staff of the study team. More details are provided under Section 11.

### **13.4. Expenses and Benefits**

Participants will be paid a sum equivalent to their day wage for their study visit as agreed by the respective ethics committees. Non-working mothers will be provided a compensation as agreeable by the respective ethics committees of Vellore and The Gambia. Reasonable travel expenses for any study-related visits will be reimbursed on production of receipts, or a mileage allowance provided as appropriate. The study participants will not have to pay for any study-related procedures (OGTT, ultrasound scans and study consultations).

### **13.5. Annual Progress Report**

The PI would submit annually, a Progress Report to the OxTREC with a copy to CTRG. Annual report will also be submitted to the funding body – The MRC, UK.

### **13.6. Other Ethical Considerations**

The study involves non-invasive measurements of the new born. Prior informed consent will be obtained from either the father or the mother to record new-born measurements. The parents of the new born will be informed that they can withdraw the consent from obtaining their child's measurements at any time point. No personal data of the new born will be collected. New-born's will be identified by a unique study identification number and linked to the mothers' research data of the mother and father's study identification number.

## **14. FINANCE AND INSURANCE**

### **14.1. Funding**

The study is funded by the Medical Research Council, UK and Global Challenges Research Fund, UK for the UK and the Gambian costs and by the Department of Biotechnology (DBT), India for the Indian costs. The Indian costs will be directly dealt between DBT and CMC, Vellore. The

Date and version No: 18th July 2019, Version 4.2

sponsor of the study is Oxford University. The funders have no role in study design; collection, management, analysis, and interpretation of data; writing of the report; and the decision to submit the report for publication.

#### **14.2. Insurance**

The University of Oxford has a specialist insurance policy in place which would operate in the event of any participant suffering harm as a result of their involvement in the research (Newline Underwriting Management Ltd, at Lloyd's of London).

#### **15. PUBLICATION POLICY**

The Investigators will be involved in reviewing drafts of the manuscripts, abstracts, press releases and any other publications arising from the study. The study will be registered and the study protocol will be made available in publically accessible websites such as ISRCTN and some national registries (Clinical Trials Registry, India). The final results of the study will be published in peer-reviewed scientific journals. Authorship will be determined in accordance with the ICMJE guidelines and other contributors will be acknowledged. For those journals that request sharing of the analyzable data sets, requests should be made to the PI-[name]. All publications will acknowledge that the study was funded by MRC, UK and DBT, India.

In order to disseminate our research findings with general public and study participants, we will engage with our communities, the wider public, the media, the broad scientific community and national and international agencies. We will explain the relevance of our research to our research participants and provide feedback of the results to them. We will use websites, the written press, TV and radio, and presentations to lay and school groups in order to ensure that our research findings reach the widest possible public audience. We will hold annual retention meetings of the study participants where results of the interim analysis and final study will be conveyed.

Date and version No: 18th July 2019, Version 4.2

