## 10. STATISTICS AND ANALYSIS

### 10.1. Description of Statistical Methods

We will analyse the study using both (1) the intention-to-treat principle and (2) per protocol, including only those participants adhering to at least 75% of the proposed intervention. In addition, we will run a sensitivity analysis to assess the effect of protocol deviation compared to 100% adherence. Analyses will be performed blinded to the intervention group allocation.

Date and version No: 18th July 2019, Version 4.2

Descriptive analysis of the first 40 participants who complete visit 2 (26-28 weeks) will be performed as advised by the funders (MRC-UK). The analysis is intended to assess feasibility, retention and adherence to all study-related procedures.

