### 12.1. DATA SAFETY MONITORING COMMITTEE (DSMC)

An independent Data Safety Monitoring Committee (DSMC) has been set up to review the progress of the trial and provide feedback to the Trial Steering Committee (TSC).

The DMC will be responsible for reviewing

- (i) general study progress (recruitment, compliance, loss to follow-up)
- (ii) clinical study safety data and assess and/or adjudicate all events of deaths
- (iii) the GDM event rate and key secondary/safety outcomes
- (iv) results of the interim analysis. The DSMC includes the following members (To address: chair of DSMC, Report preparation, confirm meeting timelines).

The DMC will review and analyze, on a regular basis, unblinded safety data throughout the study.

An independent DSMC with members who are independent from the Sponsor and the investigators for the PRIMORDIAL study comprises of experts in clinical trials/epidemiology, biostatistics and obstetrics and include the following members

| Name (Designation)                                               | Address                                                                                             | Email                                                        |
|------------------------------------------------------------------|-----------------------------------------------------------------------------------------------------|--------------------------------------------------------------|
| [name]
(Paediatrician & Postdoctoral Research Fellow) | MRC Unit The Gambia at the London School of Hygiene & Tropical Medicine, Fajara, Banjul, The Gambia | [contact]             |
| [name]
(Biostatistician)                         | MRC-LEU, University of Southampton, UK                                                              | [contact] |

Date and version No: 18th July 2019, Version 4.2

|                                     |                                                                      |                                                                          |
|-------------------------------------|----------------------------------------------------------------------|--------------------------------------------------------------------------|
| [name]
(Obstetrician) | Nuffield Department of
Obstetrics and Gynaecology,
Oxford, UK. | [contact] |

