|-------------------------------------|----------------------------------------------------------------------|--------------------------------------------------------------------------|

Meetings will be held by skype prior to start of the recruitment and then 6-monthly thereafter. The study protocol will be approved by the DSMC prior to enrolment. Any subsequent updates and implications will be reviewed periodically.

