| Interim analysis           |            |                     |            |           |         |           |         |           |
| Monitoring visits          |            |                     |            |           |         |           |         |           |
| Data quality checks        |            |                     |            |           |         |           |         |           |
| DMC meeting                |            |                     |            |           |         |           |         |           |
| Annual report preparation  |            |                     |            |           |         |           |         |           |
| Final data analysis        |            |                     |            |           |         |           |         |           |
| Preparation of manuscripts |            |                     |            |           |         |           |         |           |
| Publication of manuscripts |            |                     |            |           |         |           |         |           |
| Final report submission    |            |                     |            |           |         |           |         |           |

Date and version No: 18th July 2019, Version 4.2**20. APPENDIX C: SCHEDULE OF STUDY PROCEDURES**

| Procedures                               | Visits                    |                                  |                           |               |               |            | Delivery |
|------------------------------------------|---------------------------|----------------------------------|---------------------------|---------------|---------------|------------|----------|
|                                          | Visit -2                  | Visit -1                         | Visit 0                   | Visit 1       | Visit 2       | Visit 3    |          |
|                                          | Screening
≤16
weeks | Run-in-
phase
≤17
weeks | Randomization
Week ≤18 | Week
18-20 | Week
26-28 | Week
32 |          |
| Informed consent                         | X                         |                                  |                           |               |               |            |          |
| Eligibility assessment                   | X                         |                                  |                           |               |               |            |          |

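### Section 15 promises participants the results of an undefined interim analysis while this open-label behavioural trial may still be running, with no limit to non-comparative information

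*Protocol*

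**What the plan says.** Section 15 (Publication policy): "We will hold annual retention meetings of the study participants where results of the interim analysis and final study will be conveyed". Interim and final results are named separately. The sentence does not say what the interim results contain, and it sets no condition that follow-up be complete.

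The protocol refers to an interim analysis in two other places. Section 12.1 lists "results of the interim analysis" among the items for the DSMC, separately from general study progress and from "the GDM event rate and key secondary/safety outcomes". Appendix B has a timeline row headed "Interim analysis", whose timing cannot be read from the available text.

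Section 10.1 describes one early analysis: "Descriptive analysis of the first 40 participants who complete visit 2 (26-28 weeks) will be performed as advised by the funders". It continues: "The analysis is intended to assess feasibility, retention and adherence to all study-related procedures". Section 10.1 does not call this the interim analysis.

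Other relevant statements:
- Section 5 describes the trial as open label.
- Section 5 also says that women outside the diet arms are not asked to stop their usual dairy intake, and that step counts are hidden from women outside the PA arms.
- Section 7.5.2 hides baseline step counts so as not to influence routine activity.
- Section 7.1 recruits partly by word of mouth and, in The Gambia, through village meetings and local radio.

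**The concern.** Women know their arm, and both interventions can be adopted without the trial: yoghurt is a food and walking is free. If women heard how GDM compares between arms, some in the control margins could take up the intervention that they were not allocated, and the contrast would shrink. Adherence in the active arms could change too. Because recruitment runs partly through word of mouth and community channels, the information could also reach women who have not yet joined.

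Elsewhere the protocol treats feedback as a threat to validity: it hides step counts at baseline and in the non-PA arms. An unrestricted promise of interim results works against that safeguard, and disclosure cannot be undone. This is a stated commitment, not a detail that would normally be left to a statistical analysis plan.

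**Working it through.** **1. What the protocol fixes.** Set side by side, sections 12.1 and 15 and Appendix B name an interim analysis without content. Section 10.1 gives content (descriptive; feasibility, retention and adherence; 40 women, or 40/1856 = 2.2% of the sample) without that name. Nothing says that the two are the same, and nothing says that they differ. Section 12.1 already covers recruitment, compliance and loss to follow-up under general progress, so its separate interim item could be read as something more. The document does not settle it.

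**2. Reproducing the planned power.** The inputs come from section 10.2:
- cell risks 25%, 16.75%, 16.75% and 11.2%
- 15% of every cell reset to 25%
- each main effect tested at two-sided 2.5%
- a country-interaction pre-test at 5%
- N = 1856, so 928 women per margin

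Re-running the algorithm with 40,000 repetitions gives 80.2–80.3% power if an effect counts only when its own country interaction is non-significant. This matches the stated 80%. Without the pre-test, simulation gives 84.5% and the normal approximation 84.3%. The steps below use the approximation without the pre-test.

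**3. Adding uptake by women not allocated.** Let u be the average share of such women, among those who do not drop out, who gain the full effect of an intervention. The protocol gives no value, so u is an assumption.

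Cell risk = 0.85 × 0.25 × f₁ × f₂ + 0.15 × 0.25, where f = 0.67 if allocated and f = 1 − 0.33u if not.

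Each margin averages two cells. With p₀ and p₁ the two margin risks and p̄ their mean, power = Φ[(p₀ − p₁ − 2.241 × SE₀)/SE₁], where SE₀ = √(2p̄(1 − p̄)/928) and SE₁ = √((p₀(1 − p₀) + p₁(1 − p₁))/928).

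For u = 0:
- The cells are 0.2500, 0.1799, 0.1799 and 0.1329.
- p₀ = (0.2500 + 0.1799)/2 = 0.2149 and p₁ = (0.1799 + 0.1329)/2 = 0.1564.
- SE₀ = 0.01805 and SE₁ = 0.01800.
- Power = Φ[(0.05855 − 0.04046)/0.01800] = Φ(1.005) = 84.3%.

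| u | p₀ | p₁ | Risk ratio | Power |
|---|---|---|---|---|
| 0 | 0.2149 | 0.1564 | 0.728 | 84% |
| 0.05 | 0.2103 | 0.1552 | 0.738 | 80% |
| 0.10 | 0.2057 | 0.1540 | 0.749 | 74% |
| 0.20 | 0.1967 | 0.1517 | 0.771 | 62% |

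**4. Allowing for exposure.** If only half the women hear results before or during their intervention, 10% uptake among those exposed averages to u = 0.05 and 20% to u = 0.10. Power is then about 80% and 74%. With everyone exposed it is 74% and 62%.

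**The case against.** The strongest reply is that the harm may never arise. Section 15 does not mention comparisons between arms. If its interim analysis is the 40-woman look, participants would hear about feasibility, retention and adherence, which is close to the progress news that a retention meeting ought to give. Sections 7.4 and 10.1 also keep the trial statistician and the analyses blinded to allocation. This stands as a reason for moderation: the protocol does not say that participants will be told how the arms compare. It does not remove the point, because the sentence is unrestricted and the analysis it refers to is not identified.

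The second reply concerns size. The intervention runs from randomisation (by 18 weeks) to 32 weeks, so many women at an annual meeting will have finished, and the uptake rates have no source in the protocol. This also stands. It is why half exposure is shown beside full exposure, which is the upper end.

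A reader might go further and infer inflated type I error, since the two 2.5% tests use the whole 5% and the sample-size simulation contains no interim look. The document does not support that. It plans no interim efficacy test and no rule for claiming success early, and a descriptive look or DSMC safety review spends no alpha. A single unadjusted efficacy test at half the information would raise the per-effect error to 4.3%, but the protocol contains no such test. Any boundary could sit in a statistical analysis plan or DSMC charter that is not shown.

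**Conclusion.** The point holds as a defect in what section 15 commits to, joined to an ambiguity over which analysis is meant. Any harm is conditional on by-arm outcome information being conveyed, and its size depends on assumed uptake and exposure. For uptake of 10–20%, main-effect power would fall from about 84% to 74–62% if all women were exposed, or to 80–74% if half were. The planned power is already about 80% once the country pre-test is applied, so there is little room to absorb such a loss. These figures assume that women who take up an intervention gain its full effect; partial uptake would cost less. The correction is worth making because it is nearly free and disclosure is irreversible, not because a large loss has been shown. No claim about type I error belongs to the point.

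**What to change.** - **Section 15:** remove the reference to the interim analysis, so that the meetings convey results of the final study only. Add that, before the final analysis, participants receive only non-comparative progress information such as recruitment and retention.
- **Sections 10.1 and 12.1:** state that the interim analysis is the descriptive 40-woman feasibility analysis, and that any GDM data by arm go to the DSMC only. Use the same term in Appendix B.
- **If the sponsor intends something else:** should a comparative interim that could lead to an early claim of efficacy be planned, say so and allocate alpha to it. Otherwise the two 2.5% final tests stand unchanged.

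The cost is a wording amendment. The downside is that retention meetings can no longer present interim results.

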| Interim analysis           |            |                     |            |           |         |           |         |           |
| Monitoring visits          |            |                     |            |           |         |           |         |           |
| Data quality checks        |            |                     |            |           |         |           |         |           |
| DMC meeting                |            |                     |            |           |         |           |         |           |
| Annual report preparation  |            |                     |            |           |         |           |         |           |
| Final data analysis        |            |                     |            |           |         |           |         |           |
| Preparation of manuscripts |            |                     |            |           |         |           |         |           |
| Publication of manuscripts |            |                     |            |           |         |           |         |           |
| Final report submission    |            |                     |            |           |         |           |         |           |

Date and version No: 18th July 2019, Version 4.2**20. APPENDIX C: SCHEDULE OF STUDY PROCEDURES**

| Procedures                               | Visits                    |                                  |                           |               |               |            | Delivery |
|------------------------------------------|---------------------------|----------------------------------|---------------------------|---------------|---------------|------------|----------|
|                                          | Visit -2                  | Visit -1                         | Visit 0                   | Visit 1       | Visit 2       | Visit 3    |          |
|                                          | Screening
≤16
weeks | Run-in-
phase
≤17
weeks | Randomization
Week ≤18 | Week
18-20 | Week
26-28 | Week
32 |          |
| Informed consent                         | X                         |                                  |                           |               |               |            |          |
| Eligibility assessment                   | X                         |                                  |                           |               |               |            |          |
| Demographics                             | X                         |                                  |                           |               |               |            |          |
| History                                  | X                         |                                  |                           |               |               |            |          |
| Height                                   | X                         |                                  |                           |               |               |            |          |
| Weight                                   | X                         | X                                | X                         | X             | X             | X          | X        |
| Blood pressure                           | X                         | X                                | X                         | X             | X             | X          | X        |
| Antenatal examination                    | X                         | X                                | X                         | X             | X             | X          |          |
| Dairy consumption
questionnaire       |                           | X                                |                           |               |               |            |          |
| Barriers questionnaire                   | X                         |                                  |                           |               |               | X          |          |
| Baseline PA monitoring
with Vivofit 4 |                           | X                                |                           |               |               |            |          |
| PA step-count monitoring                 |                           |                                  | X                         | X             | X             | X          |          |
| PA assessment (Baseline)                 |                           | X                                |                           |               |               |            |          |
| Randomisation                            |                           |                                  | X                         |               |               |            |          |
| OGTT                                     | X                         |                                  |                           |               | X             |            |          |
| Dating scan                              | X                         |                                  |                           |               |               |            |          |
| Morphology scan                          |                           |                                  |                           | X             |               |            |          |
| Ultrasound scan                          |                           |                                  |                           |               |               | X          |          |
| Fasting plasma glucose                   |                           |                                  |                           |               |               | X          |          |
| Intrapartum assessment
(mother)       |                           |                                  |                           |               |               |            | X        |
| New born assessment                      |                           |                                  |                           |               |               |            | X        |

Date and version No: 18th July 2019, Version 4.2

All protocol amendments whenever a new version of the protocol is produced will be updated here.

| Amendment No. | Protocol Version No. | Date issued                   | Author(s) of changes                                                                | Details of Changes made                                                                                                                                                                                                                                                                                                                                                                                                                                                                                                                                                                                                                                                                              |
|---------------|----------------------|-------------------------------|-------------------------------------------------------------------------------------|------------------------------------------------------------------------------------------------------------------------------------------------------------------------------------------------------------------------------------------------------------------------------------------------------------------------------------------------------------------------------------------------------------------------------------------------------------------------------------------------------------------------------------------------------------------------------------------------------------------------------------------------------------------------------------------------------|
| 1             | 2.1                  | 19 th October 2018 | [name]
[name]
[name]
[name]                   | 
 
1. Stratification for risk factors during randomization (Section 7.2)
 
2. Explanations to sample size calculation (Section 10.2)
 
3. Study analysis details included under section 10.3.1 and 10.3.2
 
4. Details of DSMB included under section 12.
 
5. SAE reporting to DSMB and OxTREC is included under section 9.3.
 
6. Skin fold thickness measurement of the new born is removed from the protocol
 
7. Under Section 13,4, the following line is changed "Participants will be paid a sum equivalent to their day wage for their study visit as agreed by the respective ethics committees".
 
 |
| 2             | 3.0                  | 09 th January 2019 | [name]
[name]
[name]
[name]
[name] | 
 
1. Additional change to primary outcome measure (elevated fasting plasma glucose <math>\geq 5.1</math> mmol/l at 32 weeks GA) in Page 4
 
2. Secondary objective changed to "To determine the effect of life style intervention (yoghurt and PA), given to high-risk women from 18 weeks of gestation, on fasting blood glucose at 32 weeks (Pages 4 and 16)
 
3. Low birth weight changed to 'birth weight' under section other outcome measures in Page 5
 
                                                                                                                                                                          |

Date and version No: 18th July 2019, Version 4.2

|  |  |  |  |                                                                                                                                                                                                                                                                                                                                                                                                                                                                                                                                                                                                                                                                                                                                                                                                                                                                                                                                                                                                                                                                                                                                                                                                                                                                                                                           |
|--|--|--|--|---------------------------------------------------------------------------------------------------------------------------------------------------------------------------------------------------------------------------------------------------------------------------------------------------------------------------------------------------------------------------------------------------------------------------------------------------------------------------------------------------------------------------------------------------------------------------------------------------------------------------------------------------------------------------------------------------------------------------------------------------------------------------------------------------------------------------------------------------------------------------------------------------------------------------------------------------------------------------------------------------------------------------------------------------------------------------------------------------------------------------------------------------------------------------------------------------------------------------------------------------------------------------------------------------------------------------|
|  |  |  |  | 
4. Ponderal index and neonatal anthropometry deleted under neonatal outcomes in Pages 5, 16, 19, 27)
 
5. Run-in visit - Baseline PA will be assessed (blinded to participants) using a wearable accelerometer device (Garmin Vivofit 4 fitness band) for 7 day: to objectively measure baseline step count in all participants (Page 17)
 
6. Visit 3 (32 weeks GA, End of Study visit): morphology scan changed to ultrasound scan (Pages 17, 26)
 
7. Physical activity intervention The recommendation changed to 80% of the absolute target increase from the average target step count measured during run-in-phase (Pages 18 and 29)
 
8. Group session will use a patient participant initiative (PPI) approach where participants will be involved in designing the type of group activity, which may include activities such as group walking, dancing, stretching exercises etc. (Page 18)
 
9. Reassessment of PA activity: All participants will be asked to objectively measure step count for next 7 days using Garmin Vivofit4 at visit 2 (26-28 weeks) Women not randomized to the diet and standard care arm will have blinded assessments, while women on PA arm (PA arm or Diet+PA) will continue to achieve target step counts without blinded assessment (Page 18).
 |
|--|--|--|--|---------------------------------------------------------------------------------------------------------------------------------------------------------------------------------------------------------------------------------------------------------------------------------------------------------------------------------------------------------------------------------------------------------------------------------------------------------------------------------------------------------------------------------------------------------------------------------------------------------------------------------------------------------------------------------------------------------------------------------------------------------------------------------------------------------------------------------------------------------------------------------------------------------------------------------------------------------------------------------------------------------------------------------------------------------------------------------------------------------------------------------------------------------------------------------------------------------------------------------------------------------------------------------------------------------------------------|

Date and version No: 18th July 2019, Version 4.2

|  |  |  |  |                                                                                                                                                                                                                                                                                                                                                                                                                                                                                                                                                                                                                                                                                                                                                                                                                                                                                                                                                                                                                                                                                                                                                                                                                                                                                                                                                                                                                                                                                                       |
|--|--|--|--|-------------------------------------------------------------------------------------------------------------------------------------------------------------------------------------------------------------------------------------------------------------------------------------------------------------------------------------------------------------------------------------------------------------------------------------------------------------------------------------------------------------------------------------------------------------------------------------------------------------------------------------------------------------------------------------------------------------------------------------------------------------------------------------------------------------------------------------------------------------------------------------------------------------------------------------------------------------------------------------------------------------------------------------------------------------------------------------------------------------------------------------------------------------------------------------------------------------------------------------------------------------------------------------------------------------------------------------------------------------------------------------------------------------------------------------------------------------------------------------------------------|
|  |  |  |  | 
10. Data collection process – height and weight of father newly added (Pages 19, 21, 23-24)
 
11. Inclusion criteria changed to <math>\geq 1</math> weeks and <math>\leq 16</math> weeks of gestational age (Pages 20,23)
 
12. Inclusion criteria stamen revised as: In addition to the above, pregnant women should meet at least one of the following criteria for high-risk GDM (Page 20).
 
13. Exclusion criteria related to hypertension changed as “Currently on treatment for hypertension (pre-gestational or gestational)” (Page 20).
 
14. New exclusion criteria added: Physical disability to PA and/or known lactose intolerance (page 21).
 
15. Details of stratification at randomisation provided: Random allocation to intervention will be prestratified for age, BMI and risk factor for GDM within each study centre. We will create two age bands (<math><25</math> y and <math>\geq 25</math> years), two BMI categories (<math><25</math>, <math>\geq 26</math>) and presence of any risk factor (No 0/ Yes 1) (Page 23).
 
16. PA intervention details and 80% absolute target step count chart included in Page 29.
 
17. PA compliance definition included in Page 29 as “compliance” will be defined as will be defined as at least 80% of absolute target increase achieved on an average over 7-days period.
 
18. Statistical methods changed as “The primary analysis will be intention-to-treat. We will also
 |
|--|--|--|--|-------------------------------------------------------------------------------------------------------------------------------------------------------------------------------------------------------------------------------------------------------------------------------------------------------------------------------------------------------------------------------------------------------------------------------------------------------------------------------------------------------------------------------------------------------------------------------------------------------------------------------------------------------------------------------------------------------------------------------------------------------------------------------------------------------------------------------------------------------------------------------------------------------------------------------------------------------------------------------------------------------------------------------------------------------------------------------------------------------------------------------------------------------------------------------------------------------------------------------------------------------------------------------------------------------------------------------------------------------------------------------------------------------------------------------------------------------------------------------------------------------|

Date and version No: 18th July 2019, Version 4.2

